## 2. Study Objectives

### 2.1 Primary Objectives

#### Objectives:

The primary aim of the present study is to test the effects of the Heart-Age and Planning on Motivation to Change and Saturated Fat Intake over a period of two weeks. It is hypothesised that Heart-Age will exert its effect on motivation and planning on behaviour and that in combination they would fare better than if used independently.

To assess the above, two questionnaires will be issued:

1. Margetts et al (1989) self-report index of food
2. A two item self-perception of saturated fat intake to account for any reporting and demand characteristic biases

## 2.2 Secondary Objectives

The secondary objectives of this study is to evaluate the intervention effects on a number of social-cognitive variables e.g. intentions, self-efficacy, planning, outcome expectancies. The constructs of the HAPA model namely risk perceptions, outcome expectancies, self-efficacy and planning will be measured via questionnaires. For a diagram of the HAPA model see Appendix 8.

## 3. Study Design

### 3.1. Design and Rationale

This is a randomised, between-groups study designed to assess the difference in saturated fat intake between four different experimental conditions; a) Heart-Age and Planning, b) Heart-Age, c) Planning and d) Control Group. Subjects will be randomly allocated to one of these conditions and their responses will be measured by self-reported questionnaires. Table 2 presents the breakdown of subjects in the different conditions. Allocation to the tools will be stratified to balance by age group (30-45 years or 46-60 years), and gender.

**Table 2. Breakdown of target participant numbers in the four conditions**

| HA+Planning           |              | Heart-Age           |              | Planning            |              | Control Group       |              |
|-----------------------|--------------|---------------------|--------------|---------------------|--------------|---------------------|--------------|
| Age                   | Gender       | Age                 | Gender       | Age                 | Gender       | Age                 | Gender       |
| 30-45 years
(N=50) | Males (25)   | 30-45 years
(50) | Males (25)   | 30-45 years
(50) | Males (25)   | 30-45 years
(50) | Males (25)   |
|                       | Females (25) |                     | Females (25) |                     | Females (25) |                     | Females (25) |
| 46-60 years
(N=50) | Males (25)   | 46-60 years
(50) | Males (25)   | 46-60 years
(50) | Males (25)   | 46-60 years
(50) | Males (25)   |
|                       | Females (25) |                     | Females (25) |                     | Females (25) |                     | Females (25) |

## 4. Study Population

### 4.1 Total Number and Nature of Subjects

We will over-recruit at Time 1 to be able to take into account any drop-outs likely to occur over the study period. The aim will be to end up with 400 (or more) participants at Time 3. 100 subjects will be used for each cell of a 2x2 factorial design with the factors 'use of the Heart-Age tool' and 'use of planning'. Thus 200 subjects will use the Heart-Age site, 100 of these will plan how to reduce their saturated fat intake and the other 100 will not. Of the remaining 200 subjects, 100 will also be asked to plan how to reduce their saturated fat intake. The final 100 will act as a Control group (neither using the Heart-Age tool nor planning how to reduce their saturated fat intake).

Subjects will be recruited from both genders, be 30-60 years old and will have a high level of at least one risk factor for CHD (normally obesity). This inclusion of subjects with at least one risk factor has been deliberate. It is believed that these subjects,

though at no immediate risk of developing heart disease, will be more likely to benefit from presentation of information on their heart-health. If the information is motivating enough then they will hopefully decide to take some action to maintain or improve their future heart-health. Obese and overweight people are also expected to take into consideration their weight when making health-related judgements. Thus they should consider themselves as being at higher risk than people of average weight (Renner et al, 2000).

#### **4.2 Subject Eligibility**

Subjects will be screened by use of an online questionnaire assessing weight/height, age, gender, pre-existing cardiovascular disease and cancer.

##### **Exclusion Criteria:**

- BMI <29 (Body Mass Index)
- <30 years old
- >60 years old
- Pregnant women
- Diagnosed with cancer
- Diagnosed with a heart-condition (heart-attack or angina) – this is because algorithms predict risk of first CVD event, not recurrent events.
- Any other chronic disease of the major organs (e.g. kidney failure)
- Not willing to sign online consent form
- Not literate in use of computer and the internet
- Not being able to print at home or at work

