##### **Inclusion Criteria**

- BMI  $\geq 29$
- 30-60 years old
- Male or female
- Not diagnosed with a heart-condition (heart-attack or angina)
- Not diagnosed with cancer
- Willing to sign the Informed Consent Form
- Computer and internet literate
- Being able to print at home or at work

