### Your general health

Do you have diabetes?

☐ Yes ☐ No

Has a doctor ever told you that you have had heart disease, or have you ever had a heart attack or heart surgery?

☐ Yes ☐ No

Do you currently smoke?

☐ Yes ☐ No

Have you ever been a smoker in the past?

☐ Yes ☐ No

How long ago did you stop smoking?

years  months

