## Your family history

Your parents' medical history can give us clues about your health which will help calculate your estimated Heart Age.

Has your mother ever had heart disease? (This includes a heart attack, stroke or being diagnosed with heart disease by a doctor)

☐ Yes ☐ No ☐ I don't know

How old was your mother when she was diagnosed or had a heart attack?

Years

Has your father ever had heart disease? (This includes a heart attack, stroke or being diagnosed with heart disease by a doctor)

☐ Yes ☐ No ☐ I don't know

How old was your father when he was diagnosed or had a heart attack?

Years

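### The exclusion for a previous CVD event is narrower than its stated reason: it names only heart attack and angina, so a person with a previous stroke can enter and, in a Heart-Age arm, receive a score outside its stated scope

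*Protocol*

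**What the plan says.** The Exclusion Criteria in protocol section 4.2 rule out a diagnosed heart condition, with heart attack or angina given in brackets, and attach the reason: "this is because algorithms predict risk of first CVD event, not recurrent events". The Inclusion Criteria repeat the same two conditions: "Not diagnosed with a heart-condition (heart-attack or angina". A separate exclusion reads "Any other chronic disease of the major organs (e.g. kidney failure". The opening sentence of section 4.2 describes the screening questionnaire as assessing "weight/height, age, gender, pre-existing cardiovascular disease and cancer".

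Appendix 6 contains the screening question itself (Q8). Its options are diabetes, heart disease, high blood pressure, cancer and other chronic disease of the major organs. The second, fourth and fifth close the survey, and the screen-out list confirms that only those three do.

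In Appendix 4, the Heart-Age questionnaire asks about the participant's own history: "Has a doctor ever told you that you have had heart disease, or have you ever had a heart attack or heart surgery". For each parent it asks about heart disease with the gloss "This includes a heart attack, stroke or being diagnosed with heart disease by a doctor". Section 5.1 has this questionnaire completed in Phase 2, after allocation, by subjects going through Heart-Age.

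**The concern.** An eligibility rule should cover the people its reason covers. Here the reason is that the risk algorithms apply to people who have not yet had a CVD event. Someone with a previous stroke falls under that reason on the ordinary meaning of cardiovascular disease, but not under the wording of the heart-condition rule.

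What is at stake is the validity of personal feedback for a few individuals. By the protocol's own reasoning, the score they see is computed for a population they do not belong to. Their answers on risk perception and intention, which are secondary endpoints, would then be partly reactions to that score. The primary comparison is not seriously at risk.

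**Working it through.** The point turns on wording, and the plan states no figure to reproduce. I compared each place where the condition is defined or asked, looking for one that names stroke.

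1. **Reason for the exclusion (4.2):** first CVD event as opposed to recurrent. Scope: cardiovascular.
2. **Exclusion and inclusion wording (4.2):** heart condition, with heart attack or angina in brackets. The bracket has no e.g., whereas the chronic-disease exclusion does, so it reads as a definition and not as examples. Stroke is not named.
3. **Stated content of screening (4.2):** pre-existing cardiovascular disease. Wider than item 2 and in line with item 1.
4. **Screening question Q8 (Appendix 6):** heart disease without the bracket, so it is wider than item 2 for cardiac conditions. There is no stroke or vascular option.
5. **Catch-all (4.2 and Q8):** chronic disease of a major organ, with kidney failure as the example. A past stroke is an event and not plainly a chronic organ disease, so a lay respondent may or may not choose it. Q8 is also tagged for a single answer. If it is built that way, a stroke survivor with high blood pressure could choose that option, which does not close.
6. **Own history in the tool (Appendix 4):** heart disease, heart attack or heart surgery. Stroke is not named.
7. **Parental history in the tool (Appendix 4):** stroke is expressly counted with heart disease.

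Items 1 and 3 point one way and item 2 the other. Items 4 to 6 do not reliably close the gap. Item 7 shows that the questionnaire does count stroke with heart disease, though only for parents.

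**Size.** Section 4.1 gives 400 completers, of whom 200 use Heart-Age. The prevalence of previous stroke in this population is my assumption, 0.5% to 2%, before any screen-out through the catch-all.

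- Heart-Age users: 200 × 0.005 = 1; 200 × 0.02 = 4.
- All completers: 400 × 0.005 = 2; 400 × 0.02 = 8. Half of these are in arms that never show a score.
- At 3%, the counts would be 200 × 0.03 = 6 and 400 × 0.03 = 12.

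**Effect on the primary comparison.** If a share s of the Heart-Age users is affected, and their chance of reducing intake differs by d from what it would otherwise have been, the arm proportion moves by s × d. With s = 0.02 and an assumed d = 0.2, that is 0.02 × 0.2 = 0.004. Even the impossible extreme d = 1 gives 0.02. Section 11.3 names a difference of about 0.08 for the Heart-Age comparison.

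**The case against.** The strongest reply is that screening in practice is wider than the criterion. Q8 closes on any diagnosed heart disease, and a stroke survivor may well choose the chronic-disease option. This stands in part. It is why the claim is that such a person can enter, not that they will, and why the gap lies in non-cardiac events. It does not remove the gap, because nothing tells a respondent that a past stroke belongs under that option.

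Three stronger readings are tempting, and the documents do not support them.

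- **That people with a transient ischaemic attack or peripheral arterial disease also receive an invalid score.** The protocol never defines which events its algorithm counts, and section 1.2 describes the Framingham work largely in terms of heart disease. Only stroke is mentioned, and then as a parental risk-factor input, not as a definition of the predicted event.
- **That affected subjects are falsely reassured.** Section 1.5 says every subject receives a message pointing to their GP, and subjects with BMI above 30 can print a GP letter (diabetics excepted). The Table 1 messages for risk below 15% with BMI above 30 say that a risk factor appears elevated. Appendix 6 screens out BMI below 30, so most Heart-Age users should fall under these provisions. The score may be out of scope, but it is not delivered as an all-clear.
- **That a participant who reports heart disease in the tool is scored regardless.** Section 5.1 describes the general flow from questionnaire to score, but Appendix 4 is a paper copy of an online form and its branching is not shown. What follows a yes is unknown. Q8 should also have closed most such people out earlier.

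It is also fair to say that randomisation spreads any affected subjects over all four arms by chance, so the comparison is not biased by their entry.

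**Conclusion.** The point holds in limited form. The heart-condition exclusion is narrower than the reason given for it and narrower than the screening described in the same section, and neither the screening question nor the tool reliably makes up the difference. A person with a previous stroke can enter and, in a Heart-Age arm, receive a score outside its stated scope.

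The size is about 1 to 4 of 200 Heart-Age users, with a negligible effect on the primary comparison. This rests on two assumptions: a prevalence of 0.5% to 2%, which the documents do not give, and stroke being a CVD event for this algorithm, which the ordinary meaning and the parental item suggest but the protocol does not state. If the algorithm's definition leaves stroke out, the wording must still be reconciled, but the stroke example falls away. The case for acting is internal consistency and valid feedback for those individuals, at almost no cost.

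**What to change.** Reconcile the opening of section 4.2, its Exclusion and Inclusion Criteria, the own-history and parental-history items in Appendix 4, and Q8 with its screen-out rule in Appendix 6. Use one list of conditions in the criteria and in Q8, taken from the algorithm's own definition of a CVD event, and state that definition in the protocol. The sponsor should settle the list; stroke is the item the documents point to. Ask it at screening, before allocation, of everyone, so that a positive answer is a screen failure in all arms alike and not a discovery after randomisation in the two arms that complete the Heart-Age questionnaire.

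The cost is one criterion line, one screening option and a handful of otherwise eligible subjects: about 2 to 8 per 400 at the assumed prevalence, which the planned over-recruitment can absorb.

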##### **Inclusion Criteria**

- BMI  $\geq 29$
- 30-60 years old
- Male or female
- Not diagnosed with a heart-condition (heart-attack or angina)
- Not diagnosed with cancer
- Willing to sign the Informed Consent Form
- Computer and internet literate
- Being able to print at home or at work

#### **4.3 Restrictions and Prohibitions**

There will be no restrictions or prohibitions placed once subjects who have entered main study-phase.

### **5. Study Treatments**

#### **5.1 Study Plan**

The flow of the different study phases is seen in Figure 1 below.

Figure 1 – Study Flow

[figure not shown]

### Phase 1 – Recruitment and Screening

Recruitment will be conducted by Virtual Surveys (<http://www.virtualsurveys.com/s>), an online recruitment agency, to cost effectively reach a specific target sample within the UK population. Virtual Surveys have their own online panel and a structured script will be used to screen individuals and exclude any people who do not meet the inclusion criteria (Appendix 6). Once subjects meet the inclusion criteria, they will be acquainted with the study procedures and asked to read an online informed consent form. They will be requested to click on a number of check boxes to make sure they have read and understood the information before they proceed to the online questionnaires. Participants will out items on their perceived saturated fat intake and social-cognitive determinants.

### Phase 2 – Main study

In the main study phase, subjects will be randomly allocated into one of four different conditions: a) Heart-Age and Planning, b) Heart-age, c) Planning and d) Control Group. Those subjects going through Heart-Age will fill out a CVD assessment questionnaire. A paper copy version of the online questionnaire is found in Appendix 4. Once the CVD risk assessment questionnaire has been filled out then subjects will receive a Heart-Age score followed by brief advice on a number of lifestyle related aspects (Figure 2). Subjects in the planning condition will identify a list of situations where they would like to change their saturated fat intake. They will then be asked to match these situations with a list of behaviours. They would be requested to choose pairs of situations and behaviours that they want to change rather than ones that they are already doing (Appendix 5).

All subjects will be invited to answer a number of questions on their perceptions of the information received, intentions to make lifestyle changes, feelings of self-efficacy and expected outcomes. Subjects in the control group will only receive the questionnaires.

### Phase 3 – Study End

In the last phase, subjects will come back to the online study site to fill out a number of questionnaires. Upon completion of study, subjects will be debriefed (Appendix 8) and directed back to the Virtual Surveys site to receive payment (£15) for participation in the study and also be put in the prize draw of Amazon vouchers (£200).

### Figure 2. Heart-Age Risk Score

[figure not shown]

## 5.2 Study Assessments

Subjects will complete a number of questionnaires.

### Primary Outcome

#### Saturated Fat Intake

Self-reported amount of saturated fat intake will be measured by Margetts et al (1989) 63 item questionnaire and a two-item self-reported measure. The Margetts, Cade & Osmond (1989) questionnaire is a validated self-report index of food. The frequency of consumption of 63 common foods over the previous month using a 6-point-scale is assessed (two or more times per day; three to five times per week; one to three times per month; rarely or never). The scale has good test-retest reliability ( $r=.61$ ; Armitage & Conner, 1999).

Saturated fat intake will be also measured by a two item self perception questionnaire.

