| Study Population
Sample Size | 400 UK online users, women and men between the ages of 30-60.                                                                                                                                                                                                                                                                                                                                                                                                                                                                                                                                                                                                                                               |
| Intervention                    | An Internet based study. Volunteers will be allocated into one of four different conditions: a) Heart-Age and Planning, b) Heart-Age, c) Planning, d) Control Group. At Time 1, all subjects will be asked to fill out a set of questionnaires. At Time 2, 1 week later depending on the condition that subjects have been assigned to, they will be asked to go through Heart-Age and Planning, Heart-Age or Planning alone or to fill out a number of questionnaires on social-cognitive determinants of saturated fat intake (control group). Two weeks later, subjects will come back to the website and report on changes in their saturated fat intake and a number of social-cognitive determinants. |
| Study Endpoints                 | 
The primary endpoint is:
 
a) Intervention impact on self-reported saturated fat intake
 
The secondary endpoint is:
 
a) Intervention impact on self-efficacy, risk perceptions, intentions, outcome expectancies as measured in the HAPA model
                                                                                                                                                                                                                                                                                                                                                                                                                                      |

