## **11. Statistical Considerations**

### **11.1 Description of Statistical methods and interim analysis**

This is a randomised, stratified, between-groups study using a 2x2 factorial design with the factors 'use of the Heart-Age tool' and 'use of planning'. The primary endpoint is the change in saturated fat intake in participants allocated to the four different experimental conditions (Heart-Age and Planning, Heart-Age, Planning and Control Group). Participants will be randomly allocated to one of these four conditions, stratifying for age group (30-45 years or 46-60 years) and gender. Their saturated fat intake will be measured at baseline and the completion of the study (4 weeks after enrolment). The statistical analysis will compare the efficacy of the four treatment groups via the change in saturated fat intake between the baseline and final diet assessments. There will be no interim analyses.

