### **Foods high in saturated fat**

Eat these sorts of foods less often or in small amounts:

[figure not shown][figure not shown][figure not shown]

Red Meat, pies, sausages  
Ice-Cream  
Hard Cheese  
Chocolate  
Coconut Oil, coconut cream

Cakes & Biscuit  
Full-fat -Milk  
Pastries  
Butter & Lard

[figure not shown][figure not shown]

Please take time to carefully read and answer each question. In two weeks, you will be contacted again by email and asked to complete a brief follow-up questionnaire online.

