# SATURATED FAT INTAKE QUESTIONNAIRE

Please choose the frequency with which you have eaten each of the foods in the list below.

| Food                        | 2 or more times per day | Every day | Three to five times per week | One to two times per week | One to three times per month | Rarely or never |
|-----------------------------|-------------------------|-----------|------------------------------|---------------------------|------------------------------|-----------------|
| Whole milk                  |                         |           |                              |                           |                              |                 |
| Semi-skimmed milk           |                         |           |                              |                           |                              |                 |
| Skimmed milk                |                         |           |                              |                           |                              |                 |
| Butter                      |                         |           |                              |                           |                              |                 |
| Margarine                   |                         |           |                              |                           |                              |                 |
| Polyunsaturated margarine   |                         |           |                              |                           |                              |                 |
| Low fat spread              |                         |           |                              |                           |                              |                 |
| Ice cream                   |                         |           |                              |                           |                              |                 |
| Yoghurt                     |                         |           |                              |                           |                              |                 |
| Cheese- ordinary            |                         |           |                              |                           |                              |                 |
| Cheese- low fat             |                         |           |                              |                           |                              |                 |

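### Section 5.2 gives the primary food-frequency questionnaire a one-month recall, but it is repeated only two to three weeks after the intervention and the printed form states no recall period, so measured change may be diluted

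*Protocol*

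**What the plan says.** **Recall period.** Protocol section 5.2 (Primary Outcome) says of the FFQ: "The frequency of consumption of 63 common foods over the previous month using a 6-point-scale is assessed". The form that subjects see, in Appendix 4, opens with "Please choose the frequency with which you have eaten each of the foods in the list below" and gives no period. Only one of its six answer categories is expressed per month.

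**Timing.** The Protocol Summary places the intervention as follows: "At Time 2, 1 week later depending on the condition that subjects have been assigned to". It continues: "Two weeks later, subjects will come back to the website and report on changes in their saturated fat intake". Section 2.1 states the aim as effects on "Motivation to Change and Saturated Fat Intake over a period of two weeks", and the Time 2 instructions in Appendix 4 tell subjects "In two weeks, you will be contacted again by email and asked to complete a brief follow-up questionnaire online". Section 11.1 differs: intake is "measured at baseline and the completion of the study (4 weeks after enrolment", which is about three weeks after an intervention given at week 1. The assessment table in section 5.2 has the FFQ at Times 1 and 3 only, and section 1.4 says that the same dietary measures are repeated.

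**Second measure.** Section 5.2 also lists a two-item self-perception measure under the primary outcome. Both items, printed below the FFQ in Appendix 4, ask about the last week.

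**Analysis.** Sections 11.2 and 11.3 compare the proportion of subjects who reduced their intake. An analysis of mean reduction is optional.

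**The concern.** A follow-up questionnaire should ask about the period in which the intervention could have acted. A one-month recall reaches back past Time 2 on either of the protocol's schedules. On the three-week schedule it also reaches back past Time 1, into days that the baseline FFQ has already covered. Those days are the same in both answers and carry no information about the intervention.

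Because the form states no period, some subjects may answer for a month, some for the time since Time 2, and some for their usual diet. The choice could also differ between Time 1 and Time 3.

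At stake is the sensitivity of the main measure of the only primary endpoint. Dilution works towards no difference between arms, so a null result would be hard to interpret. No analysis can recover the recall period once the answers have been collected.

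**Working it through.** **Inputs.** Time 1 = day 0. Time 2 (intervention) = day 7 (Protocol Summary). Time 3 = day 21 (7 + 14, Protocol Summary) or day 28 (section 11.1). Recall = one month (section 5.2), taken here as 28 to 30 days, which is an assumption.

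**Share of the recall that follows the intervention** = (Time 3 − 7) / recall length.

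| Time 3 | Recall | Window | Days after Time 2 | Days before Time 2 | Days also in baseline recall |
|---|---|---|---|---|---|
| day 21 | 28 days | −7 to 21 | 14 (50%) | 14 (50%) | 7 |
| day 21 | 30 days | −9 to 21 | 14 (47%) | 16 (53%) | 9 |
| day 28 | 28 days | 0 to 28 | 21 (75%) | 7 (25%) | 0 |
| day 28 | 30 days | −2 to 28 | 21 (70%) | 9 (30%) | 2 |

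**Mean change.** If the effect starts at once and stays constant, and recall is even over the window, measured mean change = true change × share. That is 47-50% of the true change with Time 3 at day 21, and 70-75% at day 28. If subjects give recent days more weight, the loss is smaller.

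**Proportion who reduced.** This need not scale with the share, but coarse categories show how a change can disappear. Suppose a food is cut from four to two times a week at Time 2. Over 28 days ending on day 21 the average is (2 × 4 + 2 × 2) / 4 = 3 a week, which stays in the three-to-five category. A two-week recall gives 2 a week, one category lower. Reporting noise acts in the same direction: with the test-retest correlation of .61 in section 5.2, a smaller true change is more often misclassified.

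**Illustrative power.** For two proportions, two-sided 0.05, n per group, pooled variance under the null:

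power = Φ{ [d√n − 1.96√(2p̄(1−p̄))] / √(p₁(1−p₁) + p₂(1−p₂)) }

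Section 11.3's own figures come first; it states a power of 0.8 for both.

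- 10% vs 18%, n = 200: (1.131 − 0.962) / 0.487 = 0.348, power 64%.
- 10% vs 22%, n = 100: (1.200 − 1.016) / 0.511 = 0.359, power 64%.

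The stated 80% is not reproduced. Unpooled and arcsine versions give 64-65%. That is a separate matter, but it sets the starting point here.

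Now with the differences halved:

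- 10% vs 14%, n = 200: (0.566 − 0.901) / 0.459 = −0.730, power 23%.
- 10% vs 16%, n = 100: (0.600 − 0.932) / 0.474 = −0.701, power 24%.

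If 70% of each difference is kept (0.056 and 0.084; 30-day recall, Time 3 at day 28), power is 39% and 40%. If the halving is applied to an underlying normal shift instead, the differences become 0.036 and 0.052, with 20% power each.

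**The case against.** The strongest counter-argument is that the planned analysis is binary. Averaging in pre-intervention days makes a reduction smaller but does not change its sign. With error-free reporting, a true reducer would still be counted as one, and the contrast would lose nothing. This stands as a limit on the size of the problem. It does not remove the problem, because a six-category form with a test-retest correlation of .61 is not error-free.

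A reader might infer that the trial's effect is halved and that four times the sample is needed. The documents do not support that. Halving applies to mean change under the stated assumptions, and the mean analysis is optional. A reader might also start from the nominal 80% power and obtain Φ(2.80 × 0.50 − 1.96) = 29%, or 26% at a 47% share. Those are generic figures. The section 11.3 designs start at about 64%, and the true loss for the binary endpoint is unknown.

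Two further points stand. The two-item measure asks about the last week, which at Time 3 lies wholly after the intervention, so the primary outcome as a whole is not blind to the effect. It is only a partial safeguard: it is two items, covers one week, and was added to account for reporting and demand bias (section 2.1). Second, nobody can say that subjects will in fact recall a month, because the form does not ask for one. The period is unfixed, which is itself a fault.

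**Conclusion.** The inconsistency is established from the text: a one-month recall in section 5.2, no period on the form, and a follow-up two weeks after the intervention in most places but about three by section 11.1. If subjects recall 28-30 days, 50-53% of the window precedes the intervention with Time 3 at three weeks and 25-30% at four weeks. On the three-week schedule 7-9 of those days are also in the baseline recall. On neither schedule does the window lie wholly after the intervention.

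The direction is towards no effect. Mean change could lose up to about half, given an immediate, constant effect and even recall. The comparison of proportions is attenuated by an amount that the protocol does not allow one to calculate. The 23-24% power is an illustration of what halved differences would mean, not an estimate for this trial.

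**What to change.** - Print one recall window, the past two weeks, in the FFQ instruction at both Time 1 and Time 3. At Time 3 this runs from day 7 to 21 or from day 14 to 28, so it lies after the intervention on either schedule and does not overlap the baseline recall.
- Adapt the one-to-three-times-a-month answer category, and the scoring of the answers, to a two-week period.
- Amend the description of the FFQ in section 5.2 to match.
- Reconcile the four weeks after enrolment in section 11.1 with the one week plus two weeks given elsewhere, so that the protocol states a single time for the final assessment.

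**Cost.** An edit to the online form and its scoring, and a sentence each in sections 5.2 and 11.1, all before the first subject completes Time 1. The drawback is that a changed recall period and answer category depart from the published instrument, so its validation and reliability figure may not carry over exactly. The protocol should say so.
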